| The consent form was not completed on time or in its entirety                                             | For people who reported at T2 wanting sterilization as their method but did not undergo sterilization                                                                                                                                            | T3 | Dichotomous (yes/no) | Dichotomous (yes/no)                             |
| The operating room was not available                                                                      | For people who reported at T2 wanting sterilization as their method but did not undergo sterilization                                                                                                                                            | T3 | Dichotomous (yes/no) | Dichotomous (yes/no)                             |
| The wait between your delivery and getting the procedure was too long                                     | For people who reported at T2 wanting sterilization as their method but did not undergo sterilization                                                                                                                                            | T3 | Dichotomous (yes/no) | Dichotomous (yes/no)                             |
| You decided you wanted a reversible method of contraception                                               | For people who reported at T2 wanting sterilization as their method but did not                                                                                                                                                                  | T3 | Dichotomous (yes/no) | Dichotomous (yes/no)                             |

|                                               |                                                                                                              |    |                      |                                                  |
|-----------------------------------------------|--------------------------------------------------------------------------------------------------------------|----|----------------------|--------------------------------------------------|
|                                               | undergo sterilization                                                                                        |    |                      |                                                  |
| You were worried about getting anesthesia     | For people who reported at T2 wanting sterilization as their method but did not undergo sterilization | T3 | Dichotomous (yes/no) | Dichotomous (yes/no)                             |
| You were concerned about the recovery process | For people who reported at T2 wanting sterilization as their method but did not undergo sterilization | T3 | Dichotomous (yes/no) | Dichotomous (yes/no)                             |
| Other reason                                  | For people who reported at T2 wanting sterilization as their method but did not undergo sterilization | T3 | Open-ended           | Content analysis and categorization of responses |

\*Hamed Taherdoost. What Is the Best Response Scale for Survey and Questionnaire Design; Review of Different Lengths of Rating Scale / Attitude Scale / Likert Scale. *International Journal of Academic Research in Management (IJARM)*, Helvetic Editions, 2019, 8. fhal-02557308f

†Committee opinion no. 587. *ACOG Committee Opinion*. 2014;123(2):389-393. doi:10.1097/01.aog.0000443279.14017.12Hahn TA, McKenzie F, Hoffman SM, Daggy J, Tucker Edmonds B. A prospective study on the effects of Medicaid regulation and other barriers to obtaining postpartum sterilization. *Journal of Midwifery & Women's Health*. 2018;64(2):186-193. doi:10.1111/jmwh.12909

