| Ease in Contraceptive Decision Making                          | Assessed by participant responses to a 10 point scale about ease of decision making with regards to contraceptive method selection. Response options range from 0 ("Strongly Disagree" that this is an easy decision to make) to 10 ("Strongly Agree" that this is an easy decision to make").*                                                                                                                                                                                             | T1: less than 24 weeks gest.

T2: 32-36 weeks gestation | Ordinal (1-10 Likert) | Continuous (1-10)                                                                                                                                                                                                                                                                                                                                                                                              |
| Certainty about Tubal Sterilization Decision                   | Assessed by participant responses to a 10 point scale indicating certainty in desire to obtain or not obtain a tubal sterilization. Response options range from 0 ("Very Certain that I Do Not Want") to 10 ("Very Certain that I Do Want").*                                                                                                                                                                                                                                               | T1: less than 24 weeks gest.

T2: 32-36 weeks gestation | Ordinal (1-10 Likert) | We can analyze this 3 ways:

1) Nominal: 1-3 score=1 (certain about not getting it), 4-7 score=2 (uncertain), 8-10 score=3 (certain about getting it)

2) Continuous (5-10) with recoding to measure only certainty and not whether it's a certain yes or certain no:
0-->10
1--> 9
2-->8
3-->7
4-->6
5=5

3) Dichotomous: 1-3 and 8-10= 1 (certain) and 4-7=0 (uncertain) |

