- **Ease in Contraceptive Decision Making at Time 2:** Compared to women who receive usual care alone, women randomized to the decision aid arm will report greater ease in contraceptive decision making at Time 2
- **Certainty about Tubal Sterilization Decision at Time 1:** Compared to women who receive usual care alone, women randomized to the decision aid arm will report a) greater certainty about tubal sterilization decision at Time 1 and b) greater certainty in general, regardless of whether that’s for or against tubal sterilization
  - Multinomial regression (certain about not getting it vs. uncertain vs. certain about getting it) will be used to test intervention effects controlling for study site
  - Linear regression will be used (5-10, uncertain to certain) to test intervention effects controlling for study site
  - Logistic regression will be used (uncertain vs certain) to test intervention effects controlling for study site
- **Certainty about Tubal Sterilization Decision at Time 2:** Compared to women who receive usual care alone, women randomized to the decision aid arm will report a) greater certainty about tubal sterilization decision at Time 2 and b) greater certainty in general, regardless of whether that’s for or against tubal sterilization
  - Multinomial regression (certain about not getting it vs. uncertain vs. certain about getting it) will be used to test intervention effects controlling for study site
  - Linear regression will be used (5-10, uncertain to certain) to test intervention effects controlling for study site
  - Logistic regression will be used (uncertain vs certain) to test intervention effects controlling for study site
- **Participant Confidence in Contraceptive Method Selection at Time 3:** Compared to women who receive usual care alone, women randomized to the decision aid arm will report greater confidence that their current contraceptive method(s) is “right for them” at Time 3
- **Subsequent Pregnancies Since Delivery at Time 3:** Compared to women who receive usual care alone, women randomized to the decision aid arm will report lower likelihood of having a subsequent pregnancy at Time 3

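### The three coding rules for the exploratory certainty outcome cannot all be right on either a 0-10 or a 1-10 reading of the scale

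*Combined protocol and SAP*

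**What the plan says.** The row for Certainty about Tubal Sterilization Decision in Exploratory Outcome Measures gives the range in conflicting ways. The description calls the item a "10 point scale indicating certainty in desire to obtain or not obtain a tubal sterilization", and its lower anchor, at 0, is "Very Certain that I Do Not Want"; the upper anchor is at 10. The variable-structure column reads "Ordinal (1-10 Likert".

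The same row offers three codings and names no lead one:

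- Nominal: "Nominal: 1-3 score=1 (certain about not getting it), 4-7 score=2 (uncertain), 8-10 score=3 (certain about getting it".
- Folded continuous, meant to measure certainty without direction: "0-->10 1--> 9 2-->8 3-->7 4-->6 5=5", with values above 5 kept as they are.
- Dichotomous: "Dichotomous: 1-3 and 8-10= 1 (certain) and 4-7=0 (uncertain".

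Exploratory Hypotheses then uses all three at both T1 and T2: multinomial regression on the nominal version, linear regression on the fold, and for the third, "Logistic regression will be used (uncertain vs certain) to test intervention effects controlling for study site". One stated hypothesis concerns certainty irrespective of its direction. Certainty at T1 and T2 also appears among the outcomes of the pre- and post-Dobbs analyses. No section assigns a score of 0 to a category.

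**The concern.** The fold treats 0 as a valid answer carrying maximum certainty, while the two banded rules have no place for it. The fold also treats 3 and 7 as equally certain, while the banded rules separate them.

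Two things follow if the item was fielded as 0-10. First, a program that applies the banded rules literally sets answers of 0 to missing. Women would then leave two of the three models because of a response given after randomization, so the comparison is no longer between the randomized groups. Second, the dichotomous rule does not measure certainty irrespective of direction. A woman who would answer 3 rather than 7 has only changed direction, but she is counted as having become certain.

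The three analyses of one outcome could therefore disagree through coding alone. If the conflict is left open, the analyst must settle it at the time of analysis, possibly with results by arm in view.

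**Working it through.** The plan states no figure to reproduce here, so the check applies its rules to every possible answer.

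**Reading 1: the item runs 0-10, midpoint 5.**

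| Answer | Nominal | Dichotomous | Fold |
|---|---|---|---|
| 0 | none | none | 10 |
| 1 | certain not | certain | 9 |
| 2 | certain not | certain | 8 |
| 3 | certain not | certain | 7 |
| 4 | uncertain | uncertain | 6 |
| 5 | uncertain | uncertain | 5 |
| 6 | uncertain | uncertain | 6 |
| 7 | uncertain | uncertain | 7 |
| 8 | certain yes | certain | 8 |
| 9 | certain yes | certain | 9 |
| 10 | certain yes | certain | 10 |

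One of the 11 answers has no category. Mirror-image answers are x and 10 - x. The pairs 1/9, 2/8 and 4/6 are treated alike. The pair 0/10 differs by omission, and 3/7 differs by category. So two of five pairs conflict with the fold.

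**Reading 2: the item runs 1-10, midpoint 5.5.** Mirror-image answers are x and 11 - x. The banded rules now cover every answer and treat all five pairs alike (1/10, 2/9, 3/8, 4/7, 5/6). The fold fails instead: its entry for 0 can never be used, and the five pairs receive 9/10, 8/9, 7/8, 6/7 and 5/6. Each mirror pair is one point apart.

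Thus each reading repairs one part of the row and breaks another.

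**What dropping the zeros could do (reading 1).** The documents give no response distribution, so these inputs are assumptions. Let p be the true share certain in an arm, with 0 counted as certain, and z the share answering 0. After the zeros are dropped, the observed share is (p - z)/(1 - z). Take p = 60% in control and 64% in the aid arm, a true difference of 4.0 points.

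- z = 1% vs 2%: 59/99 = 59.6% and 62/98 = 63.3%; difference 3.7 points.
- z = 5% vs 12%: 55/95 = 57.9% and 52/88 = 59.1%; difference 1.2 points.
- z = 5% in both arms: 55/95 = 57.9% and 59/95 = 62.1%; difference 4.2 points.

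The attenuation depends on zeros being more common in the aid arm. With equal shares it disappears, and the difference is slightly enlarged.

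**The case against.** The strongest reply is that the item was really scored 1-10, as the structure column says and as a 10-point scale would suggest (0 to 10 has 11 values). Both banding faults then vanish. This stands as a possibility, and it is why the range should be checked against the fielded questionnaire rather than presumed. It does not clear the plan, because the stated anchors and the recode of 0 both point to 0-10, and because the fold is wrong on 1-10.

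A second reply is that 0 obviously belongs with 1-3, given that category's label. An analyst might well do this. It is unwritten, however, and it leaves the conflict between 3 and 7.

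A third reply is that little depends on it. Much of this stands. Certainty is exploratory; the four primary and secondary hypotheses and the sample size do not use it. Raw scores are collected, so nothing is lost for good. Under Inclusion Criteria all participants are contemplating sterilization, so zeros may be few.

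A reader might infer that the loss will differ by arm because the aid is expected to reduce selection of sterilization. The documents do not support that step: choosing sterilization less often does not imply moving to the extreme score, and no distribution is given. A difference by arm is possible, not shown.

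A reader might also extend the fault to Ease (same table) and to the two pregnancy-feeling items under Covariates and Baseline Characteristics, which show the same mismatch of 0-10 wording and 1-10 label. Those are analysed as continuous without cut-offs, so no answer is lost or miscoded.

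Finally, symmetry is essential for the dichotomous rule, which is meant to ignore direction. For the nominal rule, which keeps direction, completeness is essential and symmetry is closer to a preference.

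**Conclusion.** The inconsistency is real and does not depend on any assumed data: no single reading of the scale makes all three rules agree, and no other section resolves it. On the better-supported 0-10 reading, two of the three planned models at each of T1 and T2 cannot include every valid answer without an unstated decision, and the dichotomous version does not match the direction-free hypothesis it serves.

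The size of the effect on results is unknown. Under the assumed shares above with more zeros in the aid arm, the bias in a 4.0-point difference runs from 0.3 points (4.0 - 3.7) to 2.8 points (4.0 - 1.2). The upper figure needs 12% of the aid arm at the extreme of the scale. The point should be corrected because it is wrong as written and cheap to put right, but it is confined to an exploratory outcome and does not threaten the trial's main conclusions.

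**What to change.** Confirm the range actually fielded, state it consistently in the row, and fix one complete coding before looking at results by arm. If such results have already been seen, disclose when the coding was settled.

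- If 0-10: keep the fold about 5 and use symmetric bands. Either 0-2 / 3-7 / 8-10 with certain defined as a folded score of 8 or more, or 0-3 / 4-6 / 7-10 with certain defined as a folded score of 7 or more. Both are complete and agree with the fold; the choice is the sponsor's.
- If 1-10: keep the printed bands and fold about 5.5, sending x to 11 - x for answers of 5 or below. The folded score then runs from 6 to 10, so the 5-10 range in the outcome row and under the linear regressions in Exploratory Hypotheses must change too.

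For Ease and the two pregnancy-feeling items, correct only the range label.

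The cost is a few lines of text and code and no new data. The downside is that one boundary score changes category (3 becomes uncertain under the first option, 7 becomes certain under the second), or the fold is rewritten.

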### Time 2 Assessment

Study staff members will conduct Time 2 (T2) assessments by telephone between 32-36 weeks gestation to re-assess knowledge, contraceptive method selected, and decisional conflict closer to delivery and after the Medicaid sterilization consent form is typically signed. T2 follow-up contact will not exceed 4 weeks from the date of the first contact attempt. A maximum of 5 messages will be left on voicemail (2 during the first week of follow-up and one per week for remaining weeks), unless contact is established with the participant and call backs are requested. The same procedure should be followed for email. The research team will attempt to reach participant for T3 even if they did not complete T2, as long as they did not explicitly withdraw from the study.

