### Lost to Follow Up

Participants can be deemed lost to follow-up in two scenarios:

1. Once a participant has signed the consent form during their T1 appointment, they are considered “Enrolled” in this study. If a participant has been enrolled but does not complete their T1 appointment during a single session, we refer to these cases as “partial T1s.” If a partial T1 is unable to be rescheduled to complete their interview and if they do not respond to contact attempts made by research staff, they may be classified as Lost to Follow Up. [Contact attempts should be conducted according to outlined follow-up procedures above. Contact attempts may cease after 4 weeks have elapsed from missed appointment with no response from participant OR if increased gestational age would place participant outside of eligibility window for T1.]
2. If the research team is unable to reach a participant at **Time 3** after follow up protocols are followed as specified, participant may be deemed Lost to Follow Up.

**NOTE:** If a participant is unable to be reached at Time 2, they are not considered lost to follow-up and the research team should attempt to reach them again at T3. For these cases, Research staff should have this documented in their records, and then follow up procedures for T3 should be followed as specified above.

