| Proportion of intervention group participants who shared the summary sheet with their provider                                                                                                                                                    |    |    | X  |    |
| Proportion of those who signed Medicaid waiver but did not receive sterilization (calculated)                                                                                                                                                     |    |    |    | X  |
| Reason for signing consent form but not having sterilization                                                                                                                                                                                      |    |    |    | X  |
| Reason for not having sterilization (mismatch T2-T3)                                                                                                                                                                                              |    |    |    | X  |
| Reason for not having other contraceptive method (mismatch T2-T3)                                                                                                                                                                                 |    |    |    | X  |
| Shared summary sheet with provider**                                                                                                                                                                                                              |    |    | X  | X  |
| Covariates and Baseline Characteristics                                                                                                                                                                                                    |    |    |    |    |
| Future Pregnancy Desires: Do you want to get pregnant in the future?*                                                                                                                                                                             |    | X  |    |    |
| Intendedness of Current Pregnancy                                                                                                                                                                                                                 |    |    |    |    |

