| Shared summary sheet with their provider by T2/T3                                                   | After you completed the “My Decision” decision aid, you received a summary sheet. Did you ever share the summary sheet with your healthcare provider?                                                                                                                                                                                                                                                                                                                                                                                                                                                                         | T2

Again asked at T3 if participant said “No” at T2                                                            | Nominal: Yes
No
Don’t Know                                                                                                                            | Dichotomous (yes/no) [exclude Don’t Know]                                                                                                                                                                                                     |
| CALCULATED: Proportion of those who signed Medicaid waiver but DID NOT receive sterilization by T3‡ | Limit to the subgroup who signed the Medicaid sterilization waiver and consent:
“Medicaid requires that women who desire a tubal sterilization sign a consent form at least 30 days before undergoing a tubal sterilization procedure. Have you signed the Medicaid tubal sterilization consent form during this pregnancy?”

Of those who signed the consent, what proportion did NOT receive sterilization services as determined by participant responses to a multiple choice item asking which methods of contraception they have used or received since their pregnancy ended.

Denominator Description: | Medicaid sterilization consent signed:
Asked at Baseline, T2, T3

Sterilization services NOT received:
T3 | Medicaid sterilization consent signed:
i Yes
i No
i Don’t Know

Sterilization services NOT received:
multiple variables, each dichotomous | CALCULATED AS:
-among those who signed the Medicaid waiver (YES at BL, T2, or T3), what proportion DID NOT receive sterilization (operationalized as “No” on the T3 contraceptive method used question answer choice “tubal sterilization” |

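### Read literally, the summary-sheet item is repeated at T3 only after a T2 No, leaving avoidable missing answers and an undefined denominator for sharing by T2/T3

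*Combined protocol and SAP*

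**What the plan says.** The Exploratory Outcome Measures table labels the outcome "Shared summary sheet with their provider by T2/T3", which is cumulative. The item is worded to match: "Did you ever share the summary sheet with your healthcare provider". It is asked at T2, and the timing cell adds "Again asked at T3 if participant said" No at T2. The possible answers are Yes, No and Don't Know; the analysis variable is "Dichotomous (yes/no) [exclude Don’t Know".

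The follow-up sections keep women without a T2 interview in the study. Time 2 Assessment states "The research team will attempt to reach participant for T3 even if they did not complete T2", unless they have withdrawn. Lost to Follow Up states "If a participant is unable to be reached at Time 2, they are not considered lost to follow-up". Time 3 Assessment also lets a woman whose pregnancy ended before T2 go to T3 if she wishes.

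The Variables table has two rows on this subject. The row "Proportion of intervention group participants who shared the summary sheet with their provider" is marked at T2 only. The row for the item itself is marked at T2 and T3, for the intervention group only, with no skip condition.

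**The concern.** A T3 answer to an ever-shared question covers the whole period since the aid was used, whatever happened at T2. Taken at its word, the timing cell gives up that answer for two groups who can be on the telephone at T3: women never interviewed at T2, and women who were unsure at T2. The plan does not say whether these women are dropped from the proportion, counted as not having shared, or handled in some other way. Handling Missing Data is general and has no rule for this item.

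What is at stake is modest but real. Participants are encouraged to share the sheet, and providers are told in advance that patients may bring it. The sharing proportion is therefore the plan's own description of how often the aid's output reaches the clinic visit. A figure labelled as running to T2/T3 should use the T3 interviews that the protocol takes care to obtain.

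**Working it through.** **1. The plan's own figure.** None is stated for sharing. The only design number that touches this outcome is the arm size, which caps the denominator at 175. It reproduces. For d = 0.36, two-sided alpha 0.025 and 80% power, n = 2(2.241 + 0.842)²/0.36² = 147 per arm. Allowing for 15% attrition, 147/0.85 = 172.9, or 173, against 175 stated. Power with 175 × 0.85 = 148.75 per arm is 80.6%. Nothing in the sharing item alters this.

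**2. Who answers at T3 on a literal reading.**

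| T2 status | T3 condition met? | Contribution to the yes/no variable |
|---|---|---|
| Yes | No, and not needed | Yes |
| No | Yes | T2 No, updated by the T3 answer |
| Don't Know | No | Excluded |
| No T2 interview, T3 completed | No | None |
| Neither interview completed | Cannot be asked | None, under any rule |

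Rows three and four are the avoidable loss. Row five is not recoverable and is left out of what follows.

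**3. A comparison within the same table.** Medicaid consent is asked at baseline, T2 and T3 and counts as signed if the answer is Yes at any of them. That is an ever-definition with no condition on the T2 answer. The sharing item has no equivalent rule.

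**4. Possible size.** Let x be the share of reachable intervention-arm women who fall in rows three and four, p_o the sharing proportion among women with a T2 Yes or No, and p_x the proportion among the omitted women. The target is (1 − x)p_o + x·p_x.

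- Omitted women dropped: the plan reports p_o, so the error is x(p_o − p_x).
- Omitted women counted as not shared: the plan reports (1 − x)p_o, so the error is −x·p_x.
- Worst-case bounds for the target: (1 − x)p_o to (1 − x)p_o + x.

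The documents give none of x, p_o or p_x, so all the inputs below are assumptions. Take x from 5% to 20%. With the full arm of 175 as the upper limit, that is 0.05 × 175 = 8.75 to 0.20 × 175 = 35 women.

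- Dropped, sharing rates 20 points apart: 0.05 × 20 = 1.0 to 0.20 × 20 = 4.0 points. The reported figure is too high if the omitted women share less, and too low if they share more.
- Dropped, equal rates: x × 0 = 0.
- Counted as not shared, p_x from 10% to 70%: −0.05 × 10 = −0.5 to −0.20 × 70 = −14.0 points, always downward.
- Bounds at p_o = 50%: for x = 5%, 0.95 × 50 = 47.5% to 52.5%; for x = 20%, 0.80 × 50 = 40% to 60%.

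**5. The two tables side by side.** A proportion marked at T2 only is a different quantity from one labelled as running to T2/T3. T3 branching cannot affect the former and matters only for the latter. The plan does not say which is to be reported.

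**The case against.** The strongest reply is that the timing cell governs repeat questions. It does not say that a woman with no T2 interview is refused a first asking at T3, and the item row in the Variables table shows T3 with no skip condition. The questionnaires and the REDCap branching are not in the documents, so the form as built may already ask her. This stands as a limit: the omission is a literal reading of a terse cell, not a proven feature of the database. It does not remove the point, because neither table says she is asked or defines the denominator.

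A reader might infer that unsure women are never asked. They are asked at T2; they are not asked again. A reader might also infer that the reported proportion overstates use, because women who miss T2 are less engaged. The documents hold no evidence on how such women share. Dropping them could move the figure either way, and counting them as not shared would lower it.

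Two further objections hold. Some women who miss T2 will also miss T3, so the number recoverable is smaller than the number missed at T2. And the measure is descriptive: no hypothesis, model or between-arm test uses it, and the co-primary outcomes and method selected are analysed at T1. Whether to display Don't Know as its own category is a reporting preference and no part of this point.

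**Conclusion.** The point holds as a minor, cheap improvement. On a literal reading, the plan forgoes T3 answers from women with no T2 interview or a T2 Don't Know, and it leaves the denominator of the T2/T3 proportion undefined. Bias is possible, but neither its size nor its direction can be established. If 5% to 20% of reachable women are omitted and dropped, and their sharing rate differs by 20 points, the shift is 1 to 4 points either way; with equal rates it is zero. These inputs are assumed, not taken from the plan. The stronger conclusion, that the sharing proportion is biased upward, is not supported. The primary and secondary analyses and the sample size are unaffected.

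**What to change.** - At T3, ask the item of every intervention-arm woman without a T2 Yes, including those with no T2 interview and those who answered Don't Know at T2.
- Define ever shared as Yes at T2 or T3, among intervention-arm women with a Yes or No at either time, and report the number with no such answer. Under this definition a T2 No with no T3 answer counts as not shared, so give that number too.
- Reconcile the T2-only proportion row in the Variables table with the T2/T3 label in Exploratory Outcome Measures, and say which figure will be reported.

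The cost is one branching edit in REDCap and one extra question for a few women. Past-tense wording in the Variables note and in Sample Size Calculation suggests that data collection may already have been under way. For women already past T3 the edit recovers nothing; for them, report how many were not asked and show the worst-case bounds above with the observed counts.
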